**Figure 3 F3:**
[figure not shown]
Online training learning modules for implementation of BCP-VAMOS, version 3.0. Brazil. Adapted from Konrad et al. (21).

**Table 1 T1:** Description of strategies for groups with and without ongoing support for the implementation of BCP-VAMOS, version 3.0. Brazil.

**Intervention stage**	**Traditional didactic approach group^a^**	**Consultee-centered training + action planning approach group^b^**
**Program dissemination, participants enrollment**	Printed material to publicize and recruit the community: posters, flyers, and business cards.	Printed material plus guidelines to optimize dissemination and recruitment: who, where, when, and how.
**Program sections** (18 sections)	T-shirt with program logo for the provider. Digital guidelines, printed material to conduct the sections, record the frequency, and monitor and evaluate the sections.	T-shirt, manual, printed material plus guidelines for each of the sections: preparation of the site, reception, content guiding, participation registration, and individual section monitoring.
**Participants evaluation** (baseline and post-intervention)	Digital guidelines, video, and printed material to record the participants' baseline and post-intervention assessment data.	Digital guidelines, video, printed material plus guidelines for carrying out evaluations about: location, professionals involved, and the necessary care for reliable measures.

^a^20-h online training (21) + teaching materials. ^b^20-h online training (21)+ teaching materials + structured messages throughout the implementation process.

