This group will participate in the 20-h online training as described above and will receive ongoing support centered on the provider, using an action planning strategy. Ongoing support (see Table 1) will be structured by a specialist PHC researcher and provided during 12 months for all the implementation stages: recruiting the community, conducting program sessions, and evaluating participants. Support will focus on the process of identifying barriers to program implementation, selecting strategies to deal with barriers and goals for recruiting and retaining new participants. Before the start of each stage, the intervention provider will receive a message reinforcing the strategy that should be used. After each stage, another contact will be made to assess the used strategy and provide new feedback. Support will be delivered through interviews with the provider using a smartphone messaging app.

Both groups will be monitored simultaneously. If the CG providers have questions during the implementation process, these will be answered at their origin, but, being careful not to offer strategies similar like those IG will be offered. Thus, both groups will be monitored by one single researcher to avoid communication bias and to ensure that information from the IG is not passed on to the CG. This researcher will be a specialist in the health area, particularly in PHC, and received training to implement the BCP-VAMOS.

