**Reach** is a measure at the individual level of participation, which refers to the characteristics and percentages of the target population's participation in the intervention (22). In this study, reach will be assessed as the number, proportion, and representativeness of program recipients enrolled and retained in the program. We will assess the involvement of program recipients based on three reach rates: recruitment (ratio between the number of users interested in participating in the program in relation to the number of exposed users—users served at the UBS during the period when the program was announced, multiplied by 100); participation (ratio between the number of participants who will start the program in relation to the number of eligible participants in the program, multiplied by 100); retention (ratio between the number of participants who will complete and the number of participants who started the program, multiplied by 100). These reach rates will be calculated by PHC professional, comparing the IG to the CG.

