To reach the participants (recruitment), we will make available printed materials (posters, folders) and we will suggest the use of social networks, in addition to the media (radio, television, internet) to publicize the program. We recommend employing these strategies during the 30-day period prior to the start of the program. In order to recruit participants, we will establish the following eligibility criteria: being 18 years of age or older, being registered and having been attended at UBS in the 30 days prior to the start of the program (30 days from the disclosure), not meeting the minimum recommendations of PA practice (150 min per week of moderate and/or vigorous PA) and/or having inappropriate eating behavior and/or being overweight/obese and/or non-communicable chronic diseases. We will provide a questionnaire (33) and guidelines (https://vamos.ufsc.br/orientacoes-para-questionario-vamos/) to PHC professionals to screen participants. This screening will be carried out through a meeting scheduled prior to the start of the program with interested users. At this meeting, in addition to screening assessments, PHC professionals will be recommended to clarify the objectives and methodology of the program. In addition, we will assess the reasons for participants' absences and dropouts throughout the program. For this, we use the PHC professionals' monitoring records (attendance list and replacement of the sections), which will be guided to record the date and reason for the termination of each participant.

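### Participation and retention are divided by counts that the support is meant to raise, so they can favour control when the supported arm starts and completes more people; a cumulative reach measure should be added

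*Protocol article*

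**What the plan says.** The Reach paragraph under Outcomes evaluation defines three rates:

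- Recruitment: "ratio between the number of users interested in participating in the program in relation to the number of exposed users", where exposed users are those served at the health unit while the program was being announced.
- Participation: "ratio between the number of participants who will start the program in relation to the number of eligible participants in the program".
- Retention: "retention (ratio between the number of participants who will complete and the number of participants who started the program, multiplied by 100".

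It then fixes their use: "These reach rates will be calculated by PHC professional, comparing the IG to the CG". The same paragraph says, before the rates, that "reach will be assessed as the number, proportion, and representativeness of program recipients enrolled and retained in the program".

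Facilities are randomised once the professionals have finished the online training, and the program is implemented afterwards (New description, following Randomization). Community recruitment is therefore carried out under the allocated strategy. On eligibility, the plan states: "This screening will be carried out through a meeting scheduled prior to the start of the program with interested users".

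The arms differ in the help given with recruitment. In Table 1 the control group has posters, flyers and cards, while the IG has "Printed material plus guidelines to optimize dissemination and recruitment: who, where, when, and how". The description of the IG adds that its support covers "selecting strategies to deal with barriers and goals for recruiting and retaining new participants".

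**The concern.** Only the recruitment rate starts from exposed users. The retention denominator, starters, is produced after allocation and is something the IG is coached to increase. The participation denominator, eligible users, behaves in the same way if eligibility is established only among interested users who attend screening.

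If wider recruitment also brings in people who are less likely to start or finish, both rates can fall in the IG while the numbers starting and finishing rise. No rate in the plan places starters or completers over the exposed population, although the paragraph introduces reach as the share of the target population that takes part. The between-arm reach result could then point in opposite directions across the three rates, with no summary measure to settle it.

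There is a second consequence. A professional who starts no group has no starters, so retention is zero over zero and that professional leaves the comparison. The plan expects some non-adoption, since its adoption rate divides professionals who start by professionals certified. A group also needs at least 8 people to begin. Support may affect who gets that far.

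**Working it through.** **The plan's own figure.** Study location and participants gives 45 professionals × 8 people = 360 adults, which reproduces exactly. It is a recruitment expectation and says nothing about the three rates. The plan gives no expected reach rates, so the counts below are assumptions that show direction and range.

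**Condition for a reversal.** Let S be starters and C completers. With more completers in the IG, IG retention is still below CG retention whenever S_IG/S_CG > C_IG/C_CG > 1. Participation follows the same rule, with eligible users in place of S and starters in place of C.

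**Worked example.** Assumed counts per professional:

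| | CG | IG |
|---|---|---|
| Exposed | 200 | 200 |
| Interested | 20 | 40 |
| Eligible | 16 | 32 |
| Start | 12 | 20 |
| Complete | 9 | 14 |
| Recruitment | 20/200 = 10% | 40/200 = 20% |
| Participation | 12/16 = 75.0% | 20/32 = 62.5% |
| Retention | 9/12 = 75.0% | 14/20 = 70.0% |
| Starters/exposed | 12/200 = 6.0% | 20/200 = 10.0% |
| Completers/exposed | 9/200 = 4.5% | 14/200 = 7.0% |

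The IG starts 8 more people and keeps 5 more. It nevertheless scores 12.5 points lower on participation and 5 points lower on retention. Both cumulative rates rank the arms as the head counts do.

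**Range for retention.** Keep the 12 base starters completing at 75% (9 people) and add 8 IG starters who complete at rate q. IG retention is (9 + 8q)/20, against 75.0% and 9 completers in the CG.

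| q | IG completers | IG retention | Completers/exposed |
|---|---|---|---|
| 30% | 11.4 | 57.0% | 5.7% |
| 50% | 13.0 | 65.0% | 6.5% |
| 70% | 14.6 | 73.0% | 7.3% |
| 75% | 15.0 | 75.0% | 7.5% |
| 90% | 16.2 | 81.0% | 8.1% |

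**Range for participation.** Keep 16 base eligible users with 75% uptake (12 starters) and add 16 eligible users with uptake u. IG participation is (12 + 16u)/32. For u of 30%, 50%, 70%, 75% and 90% it is 52.5%, 62.5%, 72.5%, 75.0% and 82.5%, while starters run from 16.8 to 26.4 against 12 in the CG.

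**If support also improves retention of the base group.** Raise base completion to 85% and let the 8 added starters complete at 50%: (12 × 0.85 + 8 × 0.50)/20 = 14.2/20 = 71.0%. This is still below the control's 75.0%, with 14.2 completers against 9. In this setting the two arms tie when the added starters complete at 60%: (10.2 + 4.8)/20 = 75.0%.

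**The case against.** Several points on the other side have force.

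- **Counts are already mentioned.** The plan lists the number enrolled and retained as part of reach, so an excess of IG completers would probably be reported. This stands and softens the point. However, the sentence that sets the IG–CG comparison names only the rates.
- **Retention is a fair comparison in its own right.** Facilities are randomised and retention is a direct target of support. A between-arm difference in the provider's retention rate is a valid total effect on that rate, including any change in who was recruited. A reader might infer that the comparison is invalid and should lose its inference. The documents do not support that, and completers over exposed users alone could not separate keeping people from recruiting them.
- **The mechanism is assumed.** A reader might infer that wider recruitment will bring in less committed users. Nothing in the plan shows this; the eligibility criteria and the recommended explanatory meeting are common to both arms. In the range above there is no reversal at 75% completion among the added starters, and the IG is ahead at 90%.
- **The participation half depends on a reading.** The eligible count is not defined further. If it meant every eligible user of the facility, that half would not apply, although the plan describes no way to count them. The retention half holds on either reading.
- **The consequence is limited.** The primary outcomes are physical activity and eating behaviour, Table 2 gives reach a descriptive aim, and the recruitment rate already uses exposed users. Against this, the note to Table 2 and the legend of Figure 1 both use reach to judge impact between the arms.
- **Exposed users are not a perfect base.** They too are counted after allocation. The 30-day announcement period is only recommended, and IG guidance covers timing, so a longer campaign would enlarge the base. The fix has to deal with this.

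**Conclusion.** The point holds in a limited form. Retention, and participation on the more natural reading of eligible, have post-randomisation denominators that the IG-only support is meant to enlarge. Either rate can favour control while the IG starts and completes more people. In the example the gaps are 5 and 12.5 points in the wrong direction, against a gain of 2.5 points (7.0% against 4.5%) in completers over exposed users.

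These sizes rest on assumed counts. With base rates unchanged, the reversal needs added recruits to take up or complete less often than the base group; if support also improves the base group, they must fall further behind. The missing cumulative comparison and the undefined retention of professionals who start no group do not depend on those assumptions.

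Two stronger conclusions are not supported: that the trial will wrongly find that support harms retention, and that participation and retention should not be compared between arms at all.

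**What to change.** Add a cumulative measure as the main between-arm reach comparison, in one of two forms:

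- starters and completers as a proportion of exposed users, with the announcement window held at the same 30 days in both arms so that the base is comparable; or
- numbers of starters and completers per randomised facility, with facilities that start no group scored zero so that every randomised unit is kept.

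Keep participation and retention as between-arm step rates. State that they are conditional on who was recruited and are to be read beside the cumulative measure. Say also that the eligible count means those found eligible among screened interested users, if that is what is intended.

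The cost is a change of wording and one more analysis. The existing rates already require exposed users, starters and completers. Exposed users do not appear in Table 2's list of registered counts, so their recording should be made explicit. The downside is that the step rates can no longer be read alone as the effect of support on reach.

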**Figure 1 F1:**
[figure not shown]
Flow chart of procedures of the pragmatic randomized controlled trial (PRPT) for the implementation of the Active Life Improving Health Behavior Change Program (BCP-VAMOS), version 3.0, in Primary Health Care, Brazil. PHC, Primary Health Care; R, randomization; CCT+APAG, consultee-centered training plus action planning approach group; TDAG, traditional didactic approach group. ^a^The reach (R), effectiveness (E), and maintenance (M) dimensions will be considered to evaluate the impact in the implementation process between the two groups, CCT^+^APA vs. TDA. ^b^Consolidated Framework for Implementation Research.

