### New description

The randomization and allocation of health professionals into the two groups (CCT + APA vs. TDA) will be performed after all PHC professionals complete the online training. Through a randomly generated computer sequence, we will randomize each facility to one of the intervention arms with all eligible professionals within each facility randomized to the same intervention arm to avoid cross-contamination within the same facility. However, multiple facilities within the same city may be randomized to different groups. After randomization, they will be asked to implement BCP-VAMOS in their workplaces. The randomization and assignment of groups will be under the responsibility of a single researcher and will be blind to the others involved in the implementation strategies and data collection.

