**CFIR, domains**
**Intervention characteristics:** main attributes that influence the success of the intervention	**Aim:** to describe the characteristics that influence the successful implementation of the intervention. **Qualitative:** adaptability, complexity of implementation, barriers, and facilitators. *Data collection:* interview with managers, PHC professionals, and participants.
**Outer setting**: external factors of the organization can have positive or negative influences on the implementation of the intervention	**Aim:** to identify external factors that may influence the successful implementation of the intervention. **Qualitative:** perception of the patient's needs and resources for implementation. *Data collection:* interview with managers and PHC professionals.
**Inner setting**: aspects of the organization's functioning and structure that influence the success of the intervention	**Aim:** to describe the internal characteristics of the organization. **Qualitative:** climate and readiness of location/PHC professionals for implementation of the intervention. *Data collection:* interview with managers and PHC professionals.
**Characteristics of individuals**: level of knowledge, belief, attitude, and engagement of providers during implementation that may determine the success of the intervention	**Aim:** to identify personal characteristics that may influence the implementation of the intervention. **Qualitative:** knowledge and beliefs, self-efficacy, identification with the organization, and other personal attributes. *Data collection:* interview with PHC professionals.
**Process:** decision making of the organization's agents that influence the success of the intervention	**Aim:** to assess the organization's commitment to the intervention protocol. **Qualitative:** involvement of location/PHC professionals who led the intervention, barriers, and facilitators for implementation. *Data collection:* monitoring the stages and interviewing managers, PHC professionals, and participants.

PRCT, pragmatic randomized controlled trial; PA, physical activity; EB, eating behavior. ^a^These RE-AIM will be used to assess the impact of the implementation on the intervention group and control group, whose data will be collected by the PHC professionals (providers) of the intervention.

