**Effectiveness**, assessed at the individual level, refers to the extent of the intervention's impact on the primary outcomes, how it changes behavior and affects the quality of life, and whether or not there are unintended results (positive or negative) (22). In this study, effectiveness will be assessed considering the primary outcomes of BCP-VAMOS: physical activity and eating behavior. Physical activity will be assessed through a self-report of the weekly practice (type, frequency, and duration) (34) and by accelerometry (35), which allows measuring the time spent on sedentary behavior, light, moderate, and vigorous physical activity. Eating behavior will be assessed through the habit and frequency of consumption of foods classified as healthy (fruits, greens, and raw or cooked vegetables) and unhealthy (sweets, snacks, and sugary drinks) (34). These data will be collected by the PHC professionals through a validated questionnaire for the BMC-VAMOS program (33). The effectiveness outcomes will be analyzed by PHC professional (staff level) to assess the impact of intervention strategies, comparing the IG to the CG.

**Adoption** is a measure at the organizational level of participation that refers to the representativeness of locations and/or agents who are willing to implement an intervention, considering those who are eligible (22). In this study, the number, proportion, and representativeness of local/PHC professionals who initiate the program delivery will be calculated using those certified by the online training with eligibility criteria. We will calculated the adoption rate by considering the ratio between the number of PHC professionals who initiated the implementation of the program in each UBS and the number of PHC professionals certified by the online training, multiplied by 100. To identify the factors that will influence the program adoption and non-adoption, qualitative data will be collected through interviews with PHC professionals.

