**Implementation** at the organizational level refers to the degree to which delivery agents comply with several elements of an intervention protocol (22). In this study, the quality of the BCP-VAMOS implementation will be assessed based on strategies for recruiting, retaining, and monitoring participants. This analysis will be performed by PHC professional, comparing the IG to the CG. During a 1-year follow-up, a detailed manual will be developed, containing all the implemented strategies and the approximate dates for the completion of each intervention component. The manual will help in the development of checklists to assess the fidelity of the intervention delivery and the degree to which strategies are implemented as intended. A trained researcher will visit the intervention sites to observe and complete the checklist, in addition to conducting interviews with PHC professionals.

**Maintenance** at the organizational level assesses the extent to which an intervention becomes institutionalized or part of routine practices and organizational policies (22). In this study, the assessment of maintenance aims to show if new groups will be delivered during the implementation process of the BCP-VAMOS or if the local organization is interested in institutionalizing the program. This evaluation will be carried out shortly after the last section of the program, through an interview with PHC professionals and managers.

The CFIR pragmatic framework (23), widely used in implementation research in the health area (36), will be used to qualify the outcomes measures. CFIR describes 37 implementation constructs, categorized into five domains: innovation/intervention characteristics, outer setting, inner setting, characteristics of the individuals involved, and process of implementation (23).

**Innovation characteristics** directly influence the success of the implementation (36). The constructs evaluated in this domain are related to information about the *source of the intervention, quality of evidence, organizational advantage, adaptability, trialability, complexity, design and presentation of the intervention, and costs* (23). In this study, we are especially interested in adaptability—the degree to which the intervention can be customized or refined to meet local needs.

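### Reach and effectiveness are compared between arms only among professionals who start the programme, while adoption, itself a post-randomisation outcome, is never named for comparison between arms

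*Protocol article*

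**What the plan says.** All places are in the protocol article.

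- **Order of events.** Under New description, "we will randomize each facility to one of the intervention arms", and then "After randomization, they will be asked to implement BCP-VAMOS in their workplaces". The section headed Randomization gives the same order.
- **Reach.** The Reach paragraph of Outcomes evaluation defines recruitment, participation and retention rates and says "These reach rates will be calculated by PHC professional, comparing the IG to the CG". The Reach row of Table 2 specifies that the professional in question is the one delivering the programme.
- **Effectiveness.** It is analysed per professional, IG against CG. Apart from accelerometry, which a researcher collects on site, the data come from the delivering professionals.
- **Adoption.** The rate is defined as a "ratio between the number of PHC professionals who initiated the implementation of the program in each UBS and the number of PHC professionals certified". It is not split by arm and no IG–CG comparison is stated. The opening of Outcomes evaluation assigns adoption to the factors behind successful implementation, not to the impact of support.
- **Which dimensions are compared.** The Figure 1 note says that the "reach (R), effectiveness (E), and maintenance (M) dimensions will be considered to evaluate the impact in the implementation process between the two groups". Table 2 note a, attached to Reach and Effectiveness only, says "These RE-AIM will be used to assess the impact of the implementation on the intervention group and control group". The Implementation paragraph says "This analysis will be performed by PHC professional, comparing the IG to the CG".
- **What support addresses.** The support includes "selecting strategies to deal with barriers and goals for recruiting and retaining new participants" and runs from community recruitment onward.

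**The concern.** The trial asks whether ongoing support after training improves implementation. The first observable step of implementation is whether a professional starts a group at all. That step comes after allocation, so it may differ between arms because of the allocation. Any comparison confined to those who took it is a comparison of selected subgroups and no longer has the protection of randomisation.

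The documents give reason to think support could act on this step. The Introduction presents facilitation as a way to deal with barriers to adoption, and describes didactic training (the control strategy) as insufficient for wide adoption. A group needs at least 8 people to start, and support covers recruiting them. If support works mainly by getting more professionals to start, the planned contrasts in retention and behaviour change would not show it, and no stated comparison of adoption would show it either.

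**Working it through.** **1. The plan's own figure.** Study location and participants expects about 45 trained professionals and a minimum group of 8: 45 × 8 = 360, as stated. This product holds only if every trained professional starts a group. With adoption of 80%, 60% and 40% it becomes 288, 216 and 144. Non-adoption is foreseen, since the Adoption paragraph plans interviews about reasons for not adopting.

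**2. What a randomised non-adopter contributes under the stated definitions.**
- Recruitment (interested / exposed): available if the professional advertised the programme.
- Participation (started / eligible): zero if people were screened but no group began; undefined if nobody was screened.
- Retention (completed / started): 0/0, undefined.
- Behaviour change: no participants, so no result.

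Retention and effectiveness are thus conditional on adoption by construction. Read literally, the Table 2 wording makes recruitment and participation conditional too.

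**3. The lists side by side.**

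| Place | Dimensions named for comparison between arms |
|---|---|
| Figure 1 note | Reach, Effectiveness, Maintenance |
| Table 2 note a | Reach, Effectiveness |
| Outcomes text | Reach, Effectiveness, Implementation |

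Adoption appears in none.

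**4. Size, with assumed rates.** The protocol gives no adoption or retention rate, so all rates here are assumptions. With the same retention among all deliverers, and non-adopters counted as zero:

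retention per randomised professional = adoption × retention per deliverer.

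| Adoption CG / IG | Retention per deliverer CG / IG | Difference | Per randomised CG / IG | Difference |
|---|---|---|---|---|
| 50% / 50% | 60% / 60% | 0 | 30% / 30% | 0 |
| 50% / 65% | 60% / 60% | 0 | 30% / 39% | +9 points |
| 50% / 80% | 60% / 60% | 0 | 30% / 48% | +18 points |
| 60% / 90% | 60% / 60% | 0 | 36% / 54% | +18 points |
| 40% / 80% | 60% / 60% | 0 | 24% / 48% | +24 points |

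As counts, at 50% and 80% adoption with the minimum group of 8, enrolled adults per randomised professional are 8 × 0.5 = 4.0 and 8 × 0.8 = 6.4. Retained adults are 4.0 × 0.6 = 2.4 and 6.4 × 0.6 = 3.84.

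**5. Power of an adoption comparison.** Assume 22.5 professionals per arm (45 / 2; equal allocation is assumed), two-sided 5%, and independence. The normal approximation for two proportions is

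z = [d√n − 1.96√(2p̄(1 − p̄))] / √(p₁(1 − p₁) + p₂(1 − p₂)).

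For 50% against 80%: (0.30 × 4.743 − 1.96 × 0.6745) / 0.6403 = 0.158, so power is about 0.56 (Fisher's exact test with 22 and 23 per arm: 0.52). For 40% against 80% it is 0.80 (Fisher 0.77), and for 50% against 65% it is 0.17. Correlation within facilities would lower all of these.

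**The case against.** The strongest reply is that the article does not hide adoption. It is measured over all certified professionals, non-adopters are interviewed, and nothing prevents reporting it by arm. The Conclusion describes the trial as comparing implementation success between the groups. Support is listed for recruitment, sessions and evaluation, not for the decision to adopt, and manager authorisation is an inclusion criterion, so part of that decision precedes randomisation. Table 2 note a also marks which data the providers collect, so it need not be an exclusive list.

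Much of this is fair. That support affects adoption is an inference, though a reasonable one. But the article names specific dimensions for comparison in three places, differently each time, and adoption is never among them. Permission to implement is also not the same as starting.

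Three stronger readings are tempting, and the documents do not support them.

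- A reader might infer that participant drop-outs disappear from reach. They do not: retention keeps everyone who started in its denominator, and the date and reason of each termination are recorded. The paired tests under Data analysis need a post-intervention value, but handling of missing values may sit in an analysis plan not shown here.
- A reader might infer that adoption has the wrong denominator, because it uses certified professionals while randomisation follows completion of training. The two terms can be read as one milestone.
- A reader might want non-adopters scored as zero behaviour change in the main effectiveness analysis. That merges adoption with effectiveness, which RE-AIM keeps apart, and it does not fit continuous outcomes such as accelerometry time.

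**Conclusion.** The point holds in this form: the planned retention and effectiveness contrasts, and by Table 2's wording the whole reach contrast, are conditional on a post-randomisation event. That event is itself never named for comparison between arms, and the lists of compared dimensions contradict one another.

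The size depends on whether support changes adoption. Under the assumed rates the analysis per deliverer shows 0 points, while the effect per randomised professional is between +9 and +24 points (+18 for 50% against 80%). With equal adoption and equal retention both differences are 0.

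A reader might go further and infer that the plan would reverse the sign. That is arithmetically possible: if the additional IG adopters retained only 40%, the per-deliverer contrast would be (0.5 × 0.6 + 0.3 × 0.4) / 0.8 = 52.5% against 60%, or −7.5 points, against 42% and 30%, or +12, per randomised professional. Nothing in the documents suggests such a pattern, so the supportable claim is that the effect can be missed.

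**What to change.** 1. Compare adoption, IG against CG, with all randomised facilities and professionals as the denominators.
2. Add the numbers enrolled and retained per randomised facility, counting a facility that never starts as zero, as the randomised reach contrast. Counts avoid the exposed-users denominator, which is undefined at a facility that never announced the programme.
3. Keep rates among adopters and effectiveness among participants, labelled as conditional on adoption.
4. Use one list of compared dimensions, including adoption, in the Figure 1 note, Table 2 and the outcomes text.

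The cost is mainly wording: adoption, enrolment and retention are already recorded, and a non-starting facility needs no new data to be counted as zero. There are two downsides. Headline reach figures will be lower. With about 45 professionals the adoption comparison has modest power (about 0.56 for 50% against 80%, before clustering), so it should be reported as an estimate with a confidence interval and not judged by its p-value alone.
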